# Comparison of short and long forms of the Flinders program of chronic disease SELF-management for participants starting SGLT-2 inhibitors for congestive heart failure (SELFMAN-HF): protocol for a prospective, observational study

**DOI:** 10.3389/fmed.2023.1059735

**Published:** 2023-05-12

**Keywords:** congestive heart failure, Flinders program, mixed methods research methodology, protocol, risk assessment, self-management

## Abstract

**Introduction:**

Congestive heart failure (CHF) causes significant morbidity and mortality. It is an epidemic, and costs are escalating. CHF is a chronic disease whose trajectory includes stable phases, periods of decompensation, and finally palliation. Health services and medical therapies must match the various patient needs. Chronic disease self-management (CDSM) programmes that are patient-focused, identify problems and set actionable goals that appear as a logical, cost-friendly method to navigate patient journeys. There have been challenges in standardising and implementing CHF programmes.

**Methods and analysis:**

*SELFMAN-HF* is a prospective, observational study to evaluate the feasibility and validity of the *SCRinHF* tool, a one-page self-management and readmission risk prediction tool for CHF, with an established, comprehensive CDSM tool. Eligible patients will have CHF with left ventricular ejection fraction <40% and commenced sodium glucose co-transporter-2 inhibitors (SGLT2-i) within 6 months of recruitment. The primary endpoint is the 80% concordance in readmission risk predicted by the *SCRinHF* tool. The study will recruit >40 patients and is expected to last 18 months.

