### Aim and scientific hypotheses

2.1.

The *Self-management in Heart Failure Study* assesses the feasibility and validity of a short form *SCRinHF* tool (6), with the established comprehensive *Flinders Program of Chronic Disease Self-management* (Flinders Program or CFPI) (18–21) for participants who were prescribed an SGLT-2 Inhibitor for CHF. In this, we hypothesise: first, guideline level of care as established by Ref. (1, 2, 12–17), and CDSM can be used to enhance the delivery and uptake of guideline-based care (22–26); second, to achieve this, we have to define clinical pathways. In this study, the model of care is based on patients utilising community cardiologists with community-based triage (Figure 1); third, a short form CDSM tool (*SCRinHF*) will improve efficiency in delivering CDSM programmes without compromising clinical outcomes as compared to the CFPI (Figure 2). The *SELFMAN-HF* study thus aims:

To examine the relationship between CDSM and CHF-related health outcomes over a 12-month period. The CDSM tools that will be used are the CFPI and SCRinHF (Table 1). The study will establish the feasibility of use and the concurrent and predictive validity of the SCRinHF when compared to the CFPI in predicting self-management, clinical measures, and predictive measures of health outcomes (hospital readmissions) in CHF and their limitations and strength

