**Figure 2 fig2:**
[figure not shown]
Summary of standardisation structures for evidence and clinical services. **(A)** Heart failure structures for clinical standards, taxonomy domains to build systems, research methodologies to gain evidence that eventually lead to guidelines. The subsequent steps are observations on: Phase 4 translation to trial type populations, cost-effectiveness to the general population; Phase 5 is a newly coined term to explore logistics in service delivery; the final point are unknowns such as vulnerable populations, new findings that require a bench to bedside approach of gathering evidence and testing these hypotheses in a Phase 3 randomised trial. Population level. RCT – randomised controlled trial [adapted from references (1, 2, 12–16)]. **(B)** Chronic disease self-management is standardised around the Flinders Program of Chronic Disease Condition Management (CFPI). Partners in Health (PIH) are 12 self-rated questionnaire patient complete to assess self-management knowledge, attitudes, behaviours, and impacts of their chronic condition; Cue and Response Interview (C&R) is administered by health workers using an open-ended dialogue on the same questions as the PIH, and rated from the health workers perspective, and shared with the patient; Problem and Goals assessment (P&G) is health worker tool utilising behavioural psychotherapy, open-ended questions negotiate patient-identified problems and formulate goals to address them; care plan records and scores behavioural changes, monitors and progressively implements at patients pace. Barriers, strengths, and priorities identified through PIH, C&R, and P&G are incorporated into fully negotiated care plans [adapted from reference (11)]; the SCRinHF tool extracts and focuses on five domains from the CFPI. As it is a screening tool, domains tested can be re-explored should a patient be identified as at high risk and require more intensive support.

**Table 1 tab1:** SCRinHF heart failure readmission risk scoring tool.

Domains of care	Heart failure ambulatory readmission risk dimensions of care	#Yes	No	*D
1. Baseline readmission risk	Comorbid risk [Ref (1–3)]	1–3+	0	
	Managing ADL	1	0	
	Adequate Social supports	1	0	
	Compliance	1	0	
	Mood – neurovegetative, psychological [Ref (4)]	1	0	
2. Living at home (skills & goals) Self-care maintenance Self-care management Self-care confidence/efficacy	a. Do you know “how to (skill).to achieve (goal)”… [Ref (5, 6)]			

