## Study objectives

3.

The *SELFMAN-HF tests the feasibility and validity of the SCRinHF tool,* comparing the novel one-page tool to the gold standard Flinders Program of Chronic Condition Self-management Tool (CFPI). Feasibility: there are no prior comparisons of short and long form CDSM tools applied to CHF. Validity: first, this will explore comparisons of the SCRinHF to the CFPI in a range of measures including, self-management, clinical progress, and predicting 12 months major cardiovascular outcomes including readmission; and second, the Delphi method to attain peer acceptability and expert consensus on the *SCRinHF* tool.

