### End points

5.9.

The study endpoints for each phase are: Phase 1 – documentation of health journeys of patients; Phase 2 – interrogation of CFPI and SCRinHF tools for self-management capabilities and readmission risks; and Phase 3 – all data will be accumulated and discussed in the Delphi process. The primary endpoint is the readmission risk as scored by CFPI and SCRinHF and the correlation between the two tools. In addition, the following data will be collected: detailed maps of individual patient journeys and a patient and staff questionnaire on the process. Validation and times to complete the short and long forms will be recorded. The primary endpoint is 80% concordance in MACE and medical events between CFPI and SCRinHF tools. Secondary endpoints are data for cost analysis, and to inform the focus group in planning an RCT for efficacy, validity, reliability, and variability.

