### Expected outcomes

5.12.

The primary outcomes are to achieve concordance in readmission risk between CFPI and SCRinHF, and the number of patient readmissions to the hospital. The secondary outcome is to achieve convergent validity between CFPI and SCRinHF and potential economic cost benefits using the SCRinHF tool.

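### The 80% concordance endpoint is blind to the direction of disagreement, so on its own it cannot show whether SCRinHF misses patients whom the CFPI rates high-risk

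*Protocol article*

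**What the plan says.** The protocol article gives one numerical success criterion, in two places. The abstract (Methods and analysis) says "The primary endpoint is the 80% concordance in readmission risk", as predicted by SCRinHF. Section 5.9 (End points) says "The primary endpoint is 80% concordance in MACE and medical events between CFPI and SCRinHF tools". Section 5.9 also gives a non-numerical wording, "The primary endpoint is the readmission risk as scored by CFPI and SCRinHF and the correlation between the two tools", and section 5.12 (Expected outcomes) gives another: "The primary outcomes are to achieve concordance in readmission risk between CFPI and SCRinHF, and the number of patient readmissions to the hospital". None of these separates one direction of disagreement from the other or refers to sensitivity.

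Four other statements show what the comparison is for:
- Section 3 calls the CFPI the gold standard against which the one-page tool is compared.
- Section 2.1 hypothesises that the short form improves efficiency "without compromising clinical outcomes as compared to the CFPI".
- The Figure 2 legend describes SCRinHF as a screening tool and adds that "domains tested can be re-explored should a patient be identified as at high risk".
- Table 1 sorts patients into low, moderate and high readmission risk. The low band is described as able to self-manage, with reassessment twice a year. The moderate band may still receive medium- to long-term allied health support.

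**The concern.** With a reference standard in place, each disagreement has a direction: SCRinHF rates the patient either lower or higher than the CFPI does. The hypothesis in section 2.1 does not treat these alike. Rating too high mainly costs efficiency. Rating too low is the error that could compromise outcomes, and the re-exploration described in the Figure 2 legend is tied to patients identified as high risk. Percent agreement adds both errors together with equal weight.

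The criterion could therefore be met by a short form with poor sensitivity for CFPI high risk, and the result could be cited in support of the no-compromise claim when planning the RCT. This is separate from precision and from chance agreement. The limit on misses depends only on the 20% allowance and the high-risk share, so recruiting more patients does not tighten it.

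**Working it through.** **Inputs.** The pass mark is 80% (abstract; section 5.9). The minimum sample is 40 (sections 4 and 5.15). The CFPI high-risk share, p, is not stated, so it is varied over 25%, 30%, 40% and 50%. The nearest figures in the document are readmission rates of 25–50% within 1–6 months (section 1), which are only a proxy. Concordance is taken as simple percent agreement on high versus not high.

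**The plan's figure.** The 80% has no stated derivation to reproduce. At N = 40 it means 0.80 × 40 = 32 agreements, leaving 8 disagreements.

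**Step 1: the most that can be missed at exactly 80%.** If every disagreement is a CFPI high-risk patient rated lower, the missed fraction is min(1, 0.20/p).

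| p | CFPI high-risk of 40 | rated lower | fraction missed | sensitivity |
|---|---|---|---|---|
| 25% | 10 | 8 | 80% | 20% |
| 30% | 12 | 8 | 67% | 33% |
| 40% | 16 | 8 | 50% | 50% |
| 50% | 20 | 8 | 40% | 60% |

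Half or more is possible only when 0.20/p ≥ 0.50, that is, p ≤ 40%. If agreement is scored on the three bands of Table 1, the allowance is still 20%, so the ceiling is still 0.20/p.

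**Step 2: does chance correction expose it?** At p = 30%, SCRinHF rates 4/40 = 10% high. Expected agreement is 0.30 × 0.10 + 0.70 × 0.90 = 0.66. Kappa = (0.80 − 0.66)/(1 − 0.66) = 0.41. Agreement is well above chance, yet 8 of 12 high-risk patients are missed.

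**Step 3: how likely is a pass with poor sensitivity?** Assume true sensitivity 50%. True agreement is 0.50p + specificity × (1 − p). At p = 30%:
- specificity 0.95: 0.150 + 0.665 = 0.815
- specificity 0.90: 0.150 + 0.630 = 0.780
- specificity 0.80: 0.150 + 0.560 = 0.710

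The binomial probability of at least 32 agreements in 40, over all four shares, is:

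| p | specificity 0.95 | 0.90 | 0.80 |
|---|---|---|---|
| 25% | 0.81 | 0.59 | 0.19 |
| 30% | 0.69 | 0.47 | 0.14 |
| 40% | 0.41 | 0.25 | 0.07 |
| 50% | 0.19 | 0.11 | 0.03 |

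Holding the number of high-risk patients fixed, instead of letting it vary, gives 0.85, 0.71, 0.38 and 0.15 in the first column. The pattern is the same.

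**Step 4: precision of a directional estimate.** If 6 of 12 CFPI high-risk patients are also rated high, the Wilson 95% CI is 25% to 75%.

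**The case against.** The strongest reply is that this is a feasibility cohort. The article describes itself as hypothesis-generating, says the SCRinHF scoring has not been tested, and places a Delphi process and a focus group before any RCT. Nowhere does it say that reaching 80% licenses replacement of the CFPI. Concurrent and predictive validity are planned as well (section 2.1), and cross-tabulations are often left to an analysis plan. This lowers the weight of the point and argues against a pass/fail sensitivity floor: with roughly 10 to 16 high-risk patients, a floor would discriminate poorly. It does not remove the point, because the article itself fixes the 80% figure and none of the other planned analyses carries a directional criterion.

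Three stronger readings are tempting and are not supported:
- **That the tool can miss half or more without qualification.** This needs a CFPI high-risk share of 40% or less, and the share is not given. At 50% the ceiling is 40%.
- **That every patient not rated high is left to self-manage.** Table 1 still offers support to the moderate band, so high-to-low errors are only a subset of those counted in the working.
- **That only flagged patients have a safeguard.** The Figure 2 legend does not say only. Table 1 also has low-risk patients reassessed and sends acute presentations to the long form.

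It is also fair to object that concordance is undefined and that section 5.9 words the endpoint in more than one way. The calculation rests on the percent-agreement reading. The correlation wording, however, sets no limit on misses either.

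**Conclusion.** The concern holds in a conditional form. Read as percent agreement, 80% concordance is symmetric and does not test whether the short form under-rates CFPI high-risk patients, which is what the no-compromise hypothesis turns on. At exactly 80% agreement, between 40% and 80% of high-risk patients could be rated lower across shares of 50% down to 25%. These are ceilings, reached only if SCRinHF over-rates nobody.

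How likely an insensitive tool is to pass depends strongly on specificity and on the high-risk share, neither of which the document gives. At 50% sensitivity the probability runs from 0.81 (share 25%, specificity 0.95) to 0.03 (share 50%, specificity 0.80). A reader should not infer that a pass by such a tool is probable, only that the criterion does not guard against it. The point is worth acting on because it changes what a result of 80% can be said to show.

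**What to change.** Keep 80% concordance. In sections 5.9 and 5.15, add:

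1. The full low/moderate/high cross-table of CFPI against SCRinHF.
2. From that table, the proportion of CFPI high-risk patients whom SCRinHF also rates high, with its 95% CI.
3. The two directions of disagreement reported separately, with high-to-low apart from high-to-moderate.
4. Each tool's sensitivity for observed 12-month readmission, with the paired difference and its 95% CI.
5. A sentence saying that 80% overall concordance alone does not support the claim that outcomes are not compromised relative to the CFPI.

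The cost is wording in two sections and a small amount of tabulation from data already being collected, with no extra patients or procedures. The drawback is imprecision: an interval as wide as 25% to 75% will make the conclusion more cautious.

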## Patient cohort and selection criteria

4.

A minimum of 40 patients with CHF who meet the inclusion criteria will be offered an opportunity to participate. In uncertain cases, subjects will be considered eligible if the review of medical records demonstrates that they have a CHF diagnosis based on ACC/AHA and National Health Data Dictionary standardised definitions (1, 2). The project physicians will perform this. An independent physician will review uncertain cases.

Eligible patients will be: aged over 18 years; able and willing to provide informed consent; started SGLT-2i within 6 months - for systolic HF (echocardiographic EF <40%); receive one aspect of CHF care within a defined study health corridor.Patients will be excluded: If concerns are raised by any medical staff, the patient has a life expectancy of ≤6 months whilst receiving palliative or nursing home care. Cognitive status and dementia will not be a contraindication if there is consent from a caring relative or legal guardian and the ability to complete the CFPI; have a significant neurological/cognitive impairment or are unable for any reason to provide written informed consent; do not usually reside within the region (or for whom no follow-up data can be obtained); started SGLT2-i for more the >6 months.*Health Staff* will be sent surveys if they manage chronic diseases, including CHF and are willing to complete an Assessment of Chronic Illness Care (ACIC) questionnaire.

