### Statistical aspects and data analysis

5.15.

The study cohort assesses feasibility, which will allow appropriate parameters to determine sample size power calculations for future studies that will utilise a controlled design. Initial data analysis will investigate the distribution characteristics of each primary and secondary outcome measure and determine either a parametric or semi-parametric statistical approach to main data analysis. A combination of descriptive statistics, linear mixed models, and generalised estimating equations will be used to calculate and present data. If continuous outcome data are approximately normally distributed, then linear mixed models (LMMs) will be used to examine change over time for each measure at intra-and inter-individual levels. If the distribution of outcome data is more amenable to a semi-parametric approach, then we will use generalised estimating equations (GEEs) to calculate an average estimate of the intervention effect for the cohort. Descriptive statistics for baseline demographics and clinical characteristics will be presented as means (standard deviation) for continuous data and count (percent) for categorical data. As an example, the previous publication provides estimates for pilot sample size calculations for categorical data. A future RCT of 200 patients in each arm for effects size of 25% reduction in readmission at 12 months established an event rate of 1,600 readmissions at 12 months (25–50% historical rate at 1 and 6 months), 90% power, and 5% two-sided significance, and 25–75 patients are published recommendations for small to large, standardised effect sizes (30). With the introduction of SGLT-2, the population level effect size is not known, and we have chosen >40 patients with an LVEF <40% and a NYHA class of 2 or 3. The event rates are well documented as 25% for 1-month readmission and 1-year mortality. Follow-up at 12 months predicts >100 admissions and > 10 mortalities. Interim analysis will ensure that this modelling supports the study goals.

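### The 80% concordance criterion has no confidence limit and no stated allowance for chance, so about 40 patients meeting it would not show 80% agreement

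*Protocol article*

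**What the plan says.** Four statements in the protocol article bear on the primary criterion.

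- Abstract, Methods and analysis: "The primary endpoint is the 80% concordance in readmission risk predicted by the" SCRinHF tool. The comparator and the statistic are not defined there.
- Section 5.9, End points, first statement: "The primary endpoint is the readmission risk as scored by CFPI and SCRinHF and the correlation between the two tools". No threshold is given.
- Section 5.9, End points, second statement: "The primary endpoint is 80% concordance in MACE and medical events between CFPI and SCRinHF tools". This has the same threshold for a different quantity.
- Section 5.12, Expected outcomes: "The primary outcomes are to achieve concordance in readmission risk between CFPI and SCRinHF". No threshold is given.

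On size, section 4 says "A minimum of 40 patients with CHF who meet the inclusion criteria will be offered an opportunity to participate", and section 5.15 says "we have chosen >40 patients with an LVEF <40% and a NYHA class of 2 or 3". Section 5.15 supports the number with a published pilot range of 25 to 75 patients and with event rates, not with the precision of an agreement estimate. On methods, it says "A combination of descriptive statistics, linear mixed models, and generalised estimating equations will be used to calculate and present data". It describes the mixed models as serving change over time and the estimating equations as serving an average intervention effect. Table 1 gives SCRinHF three ordered risk levels (low, moderate, high). The article gives no corresponding CFPI risk levels and no expected distribution of patients over the levels of either tool.

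**The concern.** A fixed percentage used as a success mark invites a yes-or-no reading: at 80% or above, the short form is taken to be valid against the long form. Two features make that reading unsafe.

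First, a proportion from about 40 patients is imprecise, and the criterion includes no confidence limit. Tools that agree clearly less often than 80% can pass.

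Second, percent agreement includes agreement by chance, and the size of that part depends on the marginal distributions. The same 80% can be substantial agreement or little more than chance. With ordered levels, it also counts a low-versus-high disagreement the same as low-versus-moderate.

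At stake is the claim that SCRinHF has been validated against CFPI, which sections 2.1 and 3 set as an aim, and what is carried into the planned randomised trial.

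**Working it through.** The number of patients cannot be reproduced from the 80% criterion, because the article attaches no power, null value or precision to it. The check therefore asks what 80% can show with the planned number.

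**Inputs.** n = 40 (section 4 minimum; 41 as a check, since section 5.15 says more than 40). Threshold 80%, so 0.80 × 40 = 32 agreements. Concordance is read as percent agreement (assumption). Category shares are assumptions and are shown as a range.

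**1. Interval at the threshold.** Wilson, with z = 1.96 and z² = 3.84:
- centre = (0.80 + 3.84/80) / (1 + 3.84/40) = 0.848/1.096 = 0.774
- half-width = 1.96 × √(0.16/40 + 3.84/6400) / 1.096 = 0.121
- interval 65.2% to 89.5%; the exact (Clopper-Pearson) interval is 64.4% to 91.0%

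**2. Agreements needed for a lower 95% limit of 80%.** At 37/40 the Wilson lower limit is 80.1% and the exact limit 79.6%. At 38/40 the exact limit is 83.1%. So 37 (Wilson) or 38 (exact) of 40 are needed.

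**3. Chance of passing, by true agreement p.** P(X ≥ 32) with X ~ Binomial(40, p); for 41 patients, P(X ≥ 33).

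| True agreement | n = 40 | n = 41 |
|---|---|---|
| 65% | 3.0% | 2.4% |
| 70% | 11.1% | 9.4% |
| 75% | 30.0% | 27.0% |
| 80% | 59.3% | 56.2% |

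**4. Patients needed for a given precision at 80%.** n = 1.96² × 0.80 × 0.20 / h². For h = 10 points, 62; for h = 5 points, 246.

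**5. What 80% means after chance.** With equal margins on both tools, chance agreement is Pe = sum of squared shares, and unweighted kappa = (0.80 − Pe)/(1 − Pe). For example, at 80/10/10, Pe = 0.64 + 0.01 + 0.01 = 0.66 and kappa = 0.14/0.34 = 0.41. The last column is P(X ≥ 32) with p = Pe, that is, two unrelated tools.

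| Shares on both tools | Pe | Kappa at 80% | Unrelated tools reach 32/40 |
|---|---|---|---|
| three equal levels | 33.3% | 0.70 | about 0 |
| 70/20/10 | 54.0% | 0.57 | 0.06% |
| 75/25 (two levels) | 62.5% | 0.47 | 1.4% |
| 80/10/10 | 66.0% | 0.41 | 4.0% |
| 85/10/5 | 73.5% | 0.25 | 23% |
| 90/5/5 | 81.5% | below 0 | 68% |

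Steps 1 to 4 need no assumption about categories. Step 5 depends on it entirely.

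**The case against.** **Percent agreement is a reading, not a statement.** The article never says that concordance is uncorrected, and a full protocol or analysis plan could name a statistic and an interval. This stands as a limit on the claim. It does not remove the point, because the article itself fixes a numeric mark, twice, and a bare percentage is most naturally read this way. Nor do the listed methods rule out an agreement measure: percent agreement is a descriptive statistic.

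**Chance success depends on skew.** A reader might infer that two unrelated tools would commonly pass. The documents do not support this. They give no category distribution, and LVEF is not an item in Table 1, so a shared LVEF below 40% does not by itself put patients in one risk level. Recruitment is from community outpatients, and the article calls the cohort diverse. This objection stands: unrelated tools pass often only if both place roughly 85% or more of patients in one category.

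**The 59% at true agreement of exactly 80% is no defect of this sample size.** Any estimate compared with its own true value passes a little over half the time: 56% at n = 100 (80 or more) and 53% at n = 400 (320 or more). This stands, so that row is not evidence against 40 patients. Likewise, two thirds lies near the lower edge of the interval; tools at that level would pass in only about 5% of studies.

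**The study is a feasibility study.** Section 5.15 and the Discussion say so, and the closing Strengths and limitations list says that the scoring is untested and a larger study is needed. This weakens any demand for a larger sample. It does not justify a pass mark read as validation, and it favours calling the 80% descriptive.

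**Kappa has its own problems.** It is sensitive to skewed margins, and with about 40 patients its interval will be wide. This is a good reason to report kappa beside percent agreement and not to replace the criterion with a rule on kappa alone.

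**Conclusion.** The concern holds in a limited form. The protocol article makes 80% concordance its primary criterion without a confidence limit or a stated allowance for chance. If concordance means percent agreement in about 40 patients, meeting the mark exactly is compatible with true agreement from about 65% to 90%. Tools at 70% or 75% would pass in 11% or 30% of studies.

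That 80% is hard to interpret without the margins also holds: over the three-level distributions considered, it corresponds to kappa from 0.70 (equal levels) to 0.25 (85/10/5), and to less at 90/5/5. Passing by chance alone is a conditional risk, not a finding about this cohort: 23% at 85/10/5 and 68% at 90/5/5, but 4% or less at 80/10/10 and in the flatter distributions checked.

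The conclusion rests on the percent-agreement reading, 40 patients with complete scores on both tools, and, for the kappa figures, equal margins. It should be corrected before the results are interpreted, but it does not call the data collection into question.

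**What to change.** 1. Apply the criterion to one named quantity, namely readmission-risk category on both tools, and reconcile the statements in the abstract and sections 5.9 and 5.12. Set the CFPI risk categories before scoring; none is defined in the article, and without them there is no table on which to compute agreement.
2. Report percent agreement with a 95% confidence interval (Wilson or exact, named in advance). Beside it report weighted kappa with its interval and the marginal distributions of both tools, so that skew and low-versus-high disagreements are visible.
3. State that 80% on the point estimate is a descriptive feasibility target. Do not claim that the tools agree at 80% or more unless the lower confidence limit supports it, which with 40 patients means 37 (Wilson) or 38 (exact) agreements.

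This needs no extra patients. Defining the CFPI categories takes some work, but any concordance analysis requires it; the rest is slightly more analysis. The price is a less favourable claim: a result near 32/40 would be reported as an imprecise estimate that informs the next study, not as validation.
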